## Methods/design

### Setting

The MDETs in primary care sites, including independent practices, family health teams, walk-in clinics and community healthcare centers, will take place in several suburban cities and towns in Ontario. The region’s population is one of the largest with more than one million residents.

### Participants

The study involves two groups of participants: PCPs and patients assigned to their care. PCPs will be selected if they agree to refer patients with type 2 diabetes to the MDET. Patients will be included if they are ≥18 years of age, have type 2 diabetes and have an HbA1c of ≥8%. Patients who are newly diagnosed or have lived with the disease for many years are eligible because the primary treatment/management goal is to achieve glycemic control and other clinical targets to reduce the risk of complications. As such, we plan to include both prevalent and incident cases, but restrict inclusion only to patients who are at high risk (≥8%) in our research sample. Patients who have a type of diabetes that requires intense and specialized treatment, such as type 1 diabetes, gestational diabetes or patients on a complex multiple daily insulin regime, will be excluded. Ethical approval for this study has been granted by the Ryerson University Research Ethics Board, including the waiver of consent to review patient medical charts. Informed consent for all other data collection activities will be gained from all participants.

### Experimental study design

A non-blinded, cluster-randomized trial stepped wedge design will be used (see Table 
3). Findings from such a study design have been shown to generate sound scientific evidence and may better facilitate the implementation of complex health interventions in practice
[43]. We propose to randomize clusters (that is, primary care sites) and not individuals to the intervention and control group in order to minimize contamination or treatment dissemination between study groups (intervention or control). The presence of a MDET is hypothesized to affect how PCPs care for their patients; and thus, the care patients receive within the same practice site.

**Table 3 T3:** Study design – cluster randomized control trial stepped wedge design treatment schedules

**Randomization of clusters**	**Time 1**	**Time 2**	**Time 3**	**Time 4**	**Time 5**
	**0 months***	**6 months**	**12 months**	**18 months**	**24 months**
Cluster 1	1	1	1	1	1
Cluster 2	0	1	1	1	1
Cluster 3	0	0	1	1	1
Cluster 4	0	0	0	1	1

“*” represents baseline data collection across all sites prior to cluster 1 starting the intervention;

“0” represents control or existing treatment/standard care at primary care sites; “1” represents the MDET intervention; each column represents a data collection point.

Because all PCPs who expressed an interest in this study are eager to have a MDET on site, we plan to use a stepped wedge design to sequentially roll out the intervention. The time at which each cluster begins the intervention is randomized to one of the four roll-out periods (0, 6, 12, and 18 months). The randomization times are separated by six months to allow for assessment of the primary outcome (that is, HbA1c) within a reasonable time after implementation of the intervention
[13]. Clusters that are randomized into the intervention later will act as the control for the clusters who receive the intervention earlier. All clusters will subsequently receive the intervention, providing additional evidence of the intervention’s effectiveness. Using computer-generated random numbers, the team statistician blinded to the identity of the sites will randomize sites using a block randomization procedure within practice size (determined by the number of PCPs practicing at each site) as the blocking factor. Blocking on practice size will ensure that this site characteristic will be equally distributed across study groups. For the clusters receiving the intervention in the first year, 6 and 12 months of follow-up data collection have been built into the study design (18 and 24 months) to assess the sustainability of the intervention and its effects. See Table 
4 for an overview of data collection outcome measures, methods, participants and timelines.

**Table 4 T4:** Data collection outcome measures, methods, participants and timelines of evaluation study

**Outcome measures**	**Data collection method**	**Participants and timelines**
**Patient clinical outcome measures**		
Demographic and clinical information (age, sex, duration of diabetes, smoking status, comorbidity)	Patient chart data extraction	20 different randomly-selected patient charts per site, per time interval (0, 6, 12, 18 and 24 months of intervention)
Hemoglobin A1c (HbA1c)		
Low-density lipoprotein (LDL-C)		
Total cholesterol-high density lipoprotein ratio (TC-HDL ratio)		
High density lipoprotein (HDL-C)				
Diastolic blood pressure (DBP)				
Systolic blood pressure (SBP)				
Glomerular filtration rate (eGFR)				
Albumin/creatinine ratio (ACR)				
Waist circumference				
Weight				
Body mass index (BMI)				
Treatment modality				
**Primary care physician (PCP) patient care process measures**		
HbA1c, blood pressure, lipid profile, nephropathy screening (ACR and eGFR) and foot exams/tests	Patient chart data extraction	20 different randomly-selected patient charts per site, per time interval (0, 6, 12, 18 and 24 months of intervention)
Referrals for dilated retinal exam		
Provisions for or recommendations of flu vaccine		
Changes to medication		
Differences in descriptive information across PCPs	PCP questionnaire on descriptive information (that is, sex, age, years practicing, type of practice, number of diabetes patients seen per month)	All PCPs, once
Patients’ experiences and views regarding Mobile Diabetes Education Team (MDET) intervention effectiveness	Patient in-depth interviews	20 randomly-selected patients at 12 months of intervention across sites
Scheduled and attended MDET appointments	Diabetes education program charts/forms	All MDET patients, up to 2 years of intervention
**Diabetes education program (DEP) utilization outcome measures**		
PCP referrals to DEPs	Diabetes education program charts	All patients, 12 months prior to start of intervention to 12 months following start of intervention
Patients’ utilization of DEPs		
**Inter-professional collaboration (IPC) and implementation process outcome measures**		
Collaborative Practice Assessment Tool (CPAT) scores of PCPs and MDET educators	CPAT	All PCPs at 12 months of intervention
		All educators at 12 months of intervention
PCPs’ experiences and views regarding the MDET intervention implementation and IPC	PCP in-depth interviews	16 randomly-selected PCPs at 12 months of intervention across sites
MDET educators’ experiences and views regarding the MDET intervention implementation and IPC	Educator in-depth interviews	16 randomly-selected educators at 12 months of intervention across sites
	Educator reflective journals	All educators, monthly, up to 2 years of intervention
	MDET debriefing sessions	All educators, quarterly, up to 2 years of intervention

### Quantitative data collection

A repeated cross-sectional survey of patients’ medical charts will be carried out at all sites at five time intervals (0, 6, 12, 18 and 24 months). This survey entails randomly selecting charts of eligible patients who received primary care at the participating site at the time of the survey. This results in different patients being included at the five time points. Therefore, data on the demographic and clinical profile of patients will be obtained and controlled statistically prior to performing outcome comparisons between study groups. In the control sites, a 12-month retrospective data extraction will also be performed for each patient chart selected. In the intervention sites, a 12-month retrospective data extraction will be performed prior to the start of the intervention and up to 12 months during the intervention for each patient chart selected. This will be conducted to assess changes in patient care processes and clinical outcomes.

Data will be collected on:

1. Baseline demographic and clinical information (that is, age, sex, duration of diabetes, smoking status, comorbidity);

2. Treatment modality (that is, diet, oral agents, insulin, or insulin with oral agents), medical treatment, duration of insulin therapy;

3. Frequency and outcomes of tests or measures of HbA1c, LDL-C, TC-HDL; high density lipoprotein (HDL-C), diastolic and systolic blood pressure, glomerular filtration rate (eGFR), albumin/creatinine ratio (ACR), waist circumference, and weight.

The data will be extracted from patient charts for baseline comparisons between randomized clusters. For our primary hypothesis, we will collect HbA1c to assess the proportion of patients who achieve the recommended target for HbA1c (that is, HbA1C ≤7%) and assess change within patients in the intervention and between cluster groups. For our secondary hypothesis we will collect LDL-C, TC-HDL, and diastolic and systolic blood pressure to assess achievement of each of the recommended clinical targets (LDL-C <2.0 mmol/L, TC-HDL ratio < 4.0 and blood pressure <130/80 mmHg) and assess change within patients in the intervention and between cluster groups.

The proportion of patient care processes completed by PCPs over a one-year period (that is, the percentage of patients with tests for HbA1c, blood pressure, lipid profile, screening for nephropathy (ACR and eGFR), foot exams, referrals for dilated retinal exams, and provisions for or recommendations of the flu vaccine) according to clinical practice guidelines will also be collected from patient charts and compared across study groups. We also plan to document and descriptively examine changes to medication (that is, change in drug, drug dose, and addition of another drug) to assess intensification of medical management and whether the diabetes educators had an influence on PCP practices. Descriptive information (that is, sex, age, years practicing) will be collected for each PCP to further assess differences in patient care processes between study groups.

We will also calculate the percentage of patient referrals by PCPs to hosting DEPs and the onsite MDET and compare this to patients’ actual attendance at DEPs and scheduled MDET appointments. The referral rate to DEPs will be compared to the percentage of referrals from participating PCPs and their patients’ attendance at DEPs a year prior to the start of the intervention. Characteristics available in patient medical charts (that is, sex, age, duration of diabetes, clinical information and so on) will be reviewed and compared between those who were and were not referred to the MDET to better understand PCP referral practices. The number of MDET appointments planned for each patient and the number of MDET visits attended will be collected during the intervention period to examine uptake of the MDET intervention.

Various characteristics of team collaboration will be measured using the Collaborative Practice Assessment Tool (CPAT) Version 2
[27] (Office of Interprofessional Education and Practice, Queen’s University, Kingston, Ontario Canada). The CPAT survey includes 56 items across 9 domains, including mission and goals; relationships; leadership; roles, responsibilities, and autonomy; communication; decision making; conflict resolution; community linkages and coordination; and perceived effectiveness and patient involvement, which are scored 1 (strongly disagree) to 7 (strongly agree), in addition to 3 open-ended questions. Individual scores will be aggregated to create an understanding of the overall team functioning at each site. The tool will be administered to PCPs and MDET educators after 12 months of the intervention.

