### Quantitative data analysis

Specifically, for Objective #1, we will test the effectiveness of the MDET intervention on clinical outcomes (for example, HbA1C ≤ 7%, LDL-C <2.0 mmol/L) using the generalized linear mixed models (GLMM), which include site as the random effect, time as a fixed effect and the intervention effect. With the GLMM approach, the temporal trends in the effect of the intervention are also evaluated, while the correlations between patients within the same site as well as the variations between sites are accounted for (Hussey *et al.*, 2007)
[46]. The patient-level covariates (for example, age, sex, duration living with diabetes, smoking status) and PCP-level (within sites) covariates (for example, years of practice) will also be included in the model. Hierarchical linear models (HLM)
[49,50] are an important special case of GLMM, and the former name is more commonly seen in the literature for nested data structures (for example, patients at Level 1, PCPs at Level 2 and sites at Level 3). GLMM will facilitate modeling all three level variances in patient outcomes, while utilizing patient variables at Level 1, PCP variables at Level 2 and site variables at Level 3. In addition, we will consider the generalized estimating equations (GEE) approach, which has been suggested to be more robust to misspecification of the variance structure (including. correlations between patients within sites) (Hussey *et al.*, 2007)
[46]. For Objective #2, we will evaluate the effect of the MDET intervention on quality of care delivered to patients (for example, screening for ACR and eGFR) using the GLMM approach, as described for Objective #1, in addition to descriptive summaries (for example, for change in drug dose, PCP years practicing). GLMM will also be used to assess the intervention effect on, for example, the referral rate to DEPs under Objective #3, where the PCPs form the unit of the analyses, and the correlation between PCPs within sites will be taken into account along with the temporal trends of the MDET effects.

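### Objective 2: a one-year care-process score, six-month steps and one intervention effect do not fit together, and each way of filling the window at a site's first post-start survey biases the estimate

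*Protocol article*

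**What the plan says.** All of this is in the protocol article.

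- **Score.** Quantitative data collection defines the outcome as "The proportion of patient care processes completed by PCPs over a one-year period". It covers HbA1c, blood pressure and lipid tests, nephropathy screening, foot exams, retinal referral and flu vaccine.
- **Step.** Experimental study design: "The randomization times are separated by six months". The reason given there is the time needed to assess HbA1c; care processes are not mentioned.
- **Surveys.** The chart survey "will be carried out at all sites at five time intervals (0, 6, 12, 18 and 24 months").
- **Extraction.** "In the control sites, a 12-month retrospective data extraction will also be performed for each patient chart selected". For the other sites: "In the intervention sites, a 12-month retrospective data extraction will be performed prior to the start of the intervention and up to 12 months during", where that last period is time under the MDET.
- **Coding.** Table 3 codes each cluster as intervention at the survey in its own start month. Its footnote says that month 0 "represents baseline data collection across all sites prior to cluster 1 starting the intervention", yet cluster 1 is coded 1 there.
- **Model.** Quantitative data analysis evaluates Objective 2 "using the GLMM approach, as described for Objective #1, in addition to descriptive summaries". The Objective 1 model has site as a random effect, time as a fixed effect, and the intervention effect.
- **Hypothesis.** Hypothesis (ii) is stated at 12 months, and tests are made at the 1% level.

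**The concern.** The step length suits the primary outcome, but the care-process outcome needs twice that time to fill its window. At the first survey after a site starts, only six months of intervention exist. A one-year score there must either reach back six months before the start or stop at six months. In the first case a half-exposed score is counted as fully exposed. In the second, a short window is compared with a full one. Either way one pooled intervention term misstates what a year of MDET does to quality of care, and a real improvement on hypothesis (ii) could be missed or could appear as a decline.

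**Working it through.** **1. The plan's own figures.** The article gives no effect size, power or ICC for care processes. Its design figures do reproduce:
- 1,200 / (20 charts × 5 surveys) = 12 sites, or 3 per start time if the sequences are equal (implied, not stated).
- A coefficient of variation of 0.8 at a proportion of 0.5 gives a between-site variance of (0.8 × 0.5)² = 0.16. With 0.5 × 0.5 = 0.25 within sites, ICC = 0.16/0.41 = 0.39, as stated for HbA1c.

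**2. Exposed share of a one-year window ending at the survey** (starts at 0, 6, 12 and 18 months; the start-month survey taken as before the start):

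| Cluster | 0 | 6 | 12 | 18 | 24 |
|---|---|---|---|---|---|
| 1 | 0 | 0.5 | 1 | 1 | 1 |
| 2 | 0 | 0 | 0.5 | 1 | 1 |
| 3 | 0 | 0 | 0 | 0.5 | 1 |
| 4 | 0 | 0 | 0 | 0 | 0.5 |

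Cluster 4 never reaches 1.

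**3. Common one-year look-back, on/off term from the first post-start survey.** The expected estimate is the last element of (X'V⁻¹X)⁻¹X'V⁻¹μ. X holds five time indicators and the on/off term. V per site is τ²J + (0.25/20)I, with τ² = 0.25 × ICC/(1 − ICC). μ is the table above, so a full-year effect equals 1.

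| ICC | Share recovered | SE, exposure share vs on/off |
|---|---|---|
| 0.01 | 0.62 | 1.27 |
| 0.05 | 0.55 | 1.35 |
| 0.10 | 0.53 | 1.38 |
| 0.39 | 0.51 | 1.41 |

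The mean exposure of the ten cells coded on is (4 × 0.5 + 6 × 1)/10 = 0.80, so the loss is larger than simple averaging suggests. The high-ICC limit can be checked by hand. There each cell's weight is x − row mean − column mean + overall mean of the on/off table:
- The four first post-start cells have weights 0.45, 0.40, 0.35 and 0.30, which sum to 1.5.
- The six fully exposed cells have weights 0.20, −0.05, −0.30 (cluster 1), 0.15, −0.10 (cluster 2) and 0.10 (cluster 3), which sum to 0.
- The squared weights over all cells sum to 1.5.

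The estimate is (1.5 × 0.5 + 0 × 1)/1.5 = 0.50. In this limit the pooled term measures only the half-exposed survey.

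If instead a process counts as done at least once in the window, at a constant rate, recovery is 0.52 to 0.59 for one-year baselines of 0.3 to 0.7 rising by 0.09 to 0.10 (ICC 0.05 and 0.39). It is 0.62 to 0.65 for a rise from 0.5 to 0.8.

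**4. Only during-intervention time scored, not annualised.** Assume one-year probabilities of 0.5 in controls and 0.6 under the MDET, at a constant rate. The six-month probability under the MDET is 1 − √(1 − 0.6) = 0.37, set against 0.50 over twelve months in controls. At ICC 0.39 the model gives about −0.13 (on from the first post-start survey) or −0.11 (Table 3 coding), against a true +0.10. The limit in step 3 agrees: 0.37 − 0.50 = −0.13.

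**5. Table 3 coding taken literally, one-year look-back.** Start-month surveys are coded 1 with no exposed time. Recovery is 0.06, −0.13, −0.18 and −0.24 at ICC 0.01, 0.05, 0.10 and 0.39.

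**6. Alternative codings with the common window.** The exposed share as covariate recovers 1.00 at every ICC. Separate terms recover 0.50 for the first post-start survey and 1.00 for fully exposed surveys; the standard error of the latter equals that of the share model (0.058 to 0.074 over ICC 0.01 to 0.39). Dropping the half-exposed survey also recovers 1.00, with a standard error of 0.075 against 0.052 for the on/off term at ICC 0.39.

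**The case against.** A reader might infer that the plan scores pre-start months as intervention time and therefore halves the effect. The article does not say so. Its extraction rule for intervention sites separates the twelve months before the start from up to twelve months during it, so a look-back crossing the start date is only one of two readings. That point stands, and the one-half figure belongs to that reading alone. It does not clear the plan, because the other reading produces the unequal windows of step 4.

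Two further defences have some force. The article says that temporal trends in the effect are evaluated; separate terms for early and later surveys would be one ordinary way to do this and, with a common window, would recover the full-year effect. But no such term is named, and nothing ties it to the exposed part of the window. Hypothesis (ii) is also set at 12 months, when the window would be fully exposed. That makes the full-year effect the natural target, yet the single term pools half-exposed surveys with it.

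Exact exposure coding is often left to an analysis plan, which is not shown here. The point does not rest on that absence: the article itself fixes the one-year score, the six-month step and the single effect. It is also fair that the ICC of 0.39 was given for HbA1c, and that processes such as flu vaccination need not accrue evenly over a year. The first is why a range is shown, and the second bears on the choice of fix.

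**Conclusion.** The point holds in a limited form. The extraction, scoring, step and model statements for Objective 2 are not reconciled, and no reading of the window removes the bias from a single pooled effect. With a common one-year look-back coded on from the first post-start survey, about half of the full-year effect is recovered (0.51 at ICC 0.39, 0.62 at 0.01). With during-intervention time only, unequal window length can reverse the sign. Literal Table 3 coding gives roughly zero to −0.24.

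These sizes assume 12 sites in equal sequences, an immediate effect, proportional or constant-rate accrual, and a linear model standing in for the GLMM. The documents do not support a flat statement that the plan halves the effect. The matter concerns a stated objective tested at 1%, not the primary HbA1c outcome, and should be settled before the care-process data are analysed.

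**What to change.** In Quantitative data collection, state that care processes are scored over the same twelve months ending at the survey in every site, whatever its status. State also that the start-month survey, including month 0 for cluster 1, counts as unexposed if it precedes the start, and reconcile Table 3 with this.

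In Quantitative data analysis, replace the single on/off term for Objective 2 by one of:
- the share of the window that falls after the site's start (0, 0.5 or 1), which assumes linear accrual; or
- separate terms for the half-exposed first post-start survey and for fully exposed surveys, which does not.

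The second is safer for seasonal or once-a-year processes; its fully exposed term is the test of hypothesis (ii) at 12 months. Report the model without the half-exposed survey as a check.

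The cost is recoding, provided that each process is extracted with its date and that the months taken at later surveys are the twelve before the survey. The standard error of the full-year effect is 27 to 41% larger than that of the diluted on/off estimate. Under proportional accrual the ratio of effect to standard error still improves, by a factor of 1/(0.625 × 1.27) = 1.26 at ICC 0.01 and 1/(0.505 × 1.41) = 1.40 at ICC 0.39. Cluster 4 contributes no fully exposed survey, and the report should say so.

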### Scientific hypothesis

We hypothesize that the MDET intervention results in the following outcomes at 12 months:

(i) An improvement in patient clinical outcomes, primarily an increase, or greater proportion, of patients in the intervention group who are at target for HbA1c (≤7%) compared to patients in the control group.(Secondary hypothesis: an increase, or greater proportion, of patients in the intervention group who are at target for low-density lipoprotein (LDL-C) ≤2.0 mmol/L, total cholesterol-high density lipoprotein ratio (TC-HDL ratio) < 4.0, and blood pressure ≤ 130/80 mmHg, compared to patients in the control group).

(ii) An increase in the proportion of PCPs performing patient care processes, according to the Canadian clinical practice guidelines for the management of diabetes, in the intervention group compared to the control group.

(iii) An increase in the proportion of referrals to and patients’ utilization of DEPs in the intervention group compared to one year prior to the start of the intervention.

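### HbA1c testing is compared as a care-process outcome in charts that are eligible only because they hold an HbA1c result, so the tested percentage is inflated towards the ceiling, possibly unequally between groups.

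*Protocol article*

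**What the plan says.** - **Eligibility** (Participants): "Patients will be included if they are ≥18 years of age, have type 2 diabetes and have an HbA1c of ≥8" per cent.
- **Sampling** (Quantitative data collection): "This survey entails randomly selecting charts of eligible patients who received primary care at the participating site at the time of the survey". No date is given for the qualifying HbA1c relative to the survey or to the year that is scored.
- **Outcome** (Quantitative data collection): "The proportion of patient care processes completed by PCPs over a one-year period", spelled out as "the percentage of patients with tests for HbA1c, blood pressure, lipid profile, screening for nephropathy (ACR and eGFR), foot exams", followed by retinal referral and flu vaccine. These are "according to clinical practice guidelines will also be collected from patient charts and compared across study groups". Table 4 lists the same measures: "HbA1c, blood pressure, lipid profile, nephropathy screening (ACR and eGFR) and foot exams/tests".
- **Hypothesis (ii)** (Scientific hypothesis): "An increase in the proportion of PCPs performing patient care processes" in the intervention group compared with the control group.
- **Windows** (Quantitative data collection): "In the control sites, a 12-month retrospective data extraction will also be performed for each patient chart selected". Intervention-site charts have 12 months before the start and up to 12 months during the intervention.
- **Test counts**: item 3 of the data list says that the frequency and results of HbA1c tests are extracted. It does not mention test dates.

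**The concern.** A process measure for HbA1c testing should pick up patients who were not tested. Here a patient with no HbA1c result cannot enter the sample, because eligibility requires one. Nothing in the article removes the qualifying test from the count.

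Two things are at stake. First, the tested percentage is pushed upwards, which leaves less room for the increase that hypothesis (ii) predicts and makes the figure a poor description of how often these sites test. Second, control and intervention charts are searched over different windows, so the upward push need not be equal. The group comparison on this component could then reflect where the qualifying reading happens to fall rather than what the MDET does.

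**Working it through.** The article states no testing rate, power or sample size for this component, so there is no figure of its own to reproduce. The check asks how far eligibility alone moves the measure.

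**1. Size of the inflation.** Let q be the share of sampled charts whose qualifying HbA1c lies inside the scored year, and t the chance of a test in that year otherwise. If any one test counts:

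observed proportion tested = q + (1 − q) × t

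The documents give neither q nor t, so both are assumptions shown as ranges.

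| q | t = 0.6 | t = 0.7 | t = 0.8 | t = 0.9 |
|---|---|---|---|---|
| 1 | 100% | 100% | 100% | 100% |
| 0.9 | 96% | 97% | 98% | 99% |
| 0.75 | 90% | 92.5% | 95% | 97.5% |
| 0.5 | 80% | 85% | 90% | 95% |
| 0 | 60% | 70% | 80% | 90% |

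Example: q = 0.9 and t = 0.6 give 0.9 + 0.1 × 0.6 = 0.96.

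**2. What the inflation does to detectability.** Inputs from Statistical analysis: 20 charts per site per time, 1,200 in total, five times, hence 1,200 / (20 × 5) = 12 sites (implied, not stated); ICC 0.39; significance level 1%. Assumptions: three sites per sequence, two-sided test, the same ICC for this outcome, and an intervention rate at its maximum of 100%. The stepped-wedge variance of Hussey and Hughes is

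Var = I σ² (σ² + T τ²) / [(I U − W) σ² + (U² + I T U − T W − I V) τ²]

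Here I = 12 and T = 5. U is the number of intervention site-periods, W the sum of squared column totals and V the sum of squared row totals of the treatment schedule. With p̄ the mean of the control rate and 100%, σ² = p̄(1 − p̄)/20 and τ² = (0.39/0.61) p̄(1 − p̄). Table 3 marks the first cluster as treated at month 0 but also calls that column baseline. Both codings give the same variance (U = 42, W = 414, V = 162, or U = 30, W = 270, V = 90).

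For a control rate of 98%: p̄ = 0.99, σ² = 0.000495, τ² = 0.00633, SE = 0.0104. The largest possible gain is 0.02, so z = 0.02/0.0104 = 1.92, and power = Φ(1.92 − 2.576) = about 0.26.

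| Control rate | Largest possible gain | Power for that gain |
|---|---|---|
| 90% | 10 points | 0.96 |
| 95% | 5 points | 0.68 |
| 97% | 3 points | 0.41 |
| 98% | 2 points | 0.26 |
| 99% | 1 point | 0.11 |
| 100% | 0 | none possible |

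The normal approximation is rough this close to 100%; the table shows the pattern rather than exact values.

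**3. Unequal windows.** Suppose the qualifying reading lies inside the single retrospective year for control charts (q = 1) but in the pre-start year for intervention charts, and the year during the intervention is the one scored (q = 0). Then control = 100%, intervention = t, and the difference is t − 1:

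- t = 1.0: 0
- t = 0.95: −5 points
- t = 0.9: −10 points
- t = 0.8: −20 points
- t = 0.7: −30 points

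This gap comes from selection and windows alone.

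**The case against.** The strongest reply is that the article does not date the qualifying reading and does not say that any single test is a pass. Processes are judged against practice guidelines and test frequency is extracted, so scoring against a required number of tests remains open. If readings can fall outside the scored year, the rate could lie well below the ceiling, and from a control rate of 90% the largest possible gain has power of about 0.96. Exact scoring rules are also what a condensed article leaves to its full protocol.

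Most of this stands as a limit on the point. A reader might infer that the component must sit at 100% in both groups and cannot show an effect. The documents do not support that, because it needs the qualifying reading inside the scored year in both groups and an any-test rule, and neither is stated. A reader might also infer that a constant item dilutes a pooled process score by one seventh, about 14%. No passage pools the seven processes; and if they were averaged, a constant item would multiply the difference and its standard error alike by 6/7, leaving power unchanged.

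What the reply does not remove is the overlap itself. The article states both the entry criterion and the outcome, and nothing in it separates them. Under frequency scoring, a qualifying test inside the window still counts as one of the required tests.

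**Conclusion.** The point holds in limited form. HbA1c testing is compared across groups in a sample selected on having an HbA1c result, so the tested percentage is inflated towards the ceiling. It is exactly 100% where the qualifying reading lies in the scored year and one test suffices, and 96% to 99% if 90% of readings do so (t from 0.6 to 0.9). At control rates of 98% to 99%, power for even the largest possible gain is about 0.26 to 0.11, given 12 implied sites, ICC 0.39 and a two-sided 1% level. Because the extraction windows differ, the inflation may be unequal, with an artificial difference of 0 to −30 points in the scenario worked above. How much of this occurs depends on the timing of the qualifying reading, which the article does not give.

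The problem is confined to one component of a non-primary hypothesis. No matching entry criterion applies to blood pressure, lipids, nephropathy screening, foot exams, retinal referral or flu vaccine. It should be corrected, but it does not bear on the primary outcome.

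**What to change.** In Quantitative data collection and Table 4:

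1. Record the date of each chart's qualifying HbA1c.
2. Score HbA1c testing over a window of the same length and definition in both conditions.
3. Leave the qualifying test out of the count.
4. Score this component only in charts whose extracted data cover the full window. The last condition matters because a follow-up interval starting at a recent qualifying reading can run past the control charts' 12-month retrospective extraction, and such charts would wrongly appear untested.

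If the extracted data cannot support this, take HbA1c testing out of the processes tested under hypothesis (ii) and report it descriptively, stating that eligibility constrains it.

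Cost: the reported HbA1c-testing rate will be lower, index dates must be abstracted (the article names frequency and results, not dates), and some charts may not contribute to this component. The design, the site sample and the other process measures are unchanged.
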